### Analysis

Descriptive summaries of socio-demographic information will be provided for baseline, and follow up time-points for the sample as appropriate. Descriptive summaries at the level of IAPT services will also be provided. Missing data will be reported for all treatment time-points to describe retention/drop-out rates. Reasons for drop-out will be recorded. We will use the STROBE statement (http://www.strobe-statement.org/index.php?id = available-checklists) for a list of items to be reported. All statistical analyses will be carried out in the statistical software package STATA. Descriptive summaries for all outcome measures will be provided. Continuous outcome measures will be inspected visually to assess the normality of data and to check for outliers. Univariate associations with IAPT non-recovery will be explored using t-tests (for normally distributed data) and Mann-Whitney tests (for skewed data). The independence of associations between the proposed predictor variables and IAPT non-response will be explored using linear mixed model methods (for continuous outcome measures) and logistic regression (for categorically-defined outcomes i.e. recovered vs. non-recovered). The possibility of sex interactions and non-linear effects will be examined. Analysis of residuals from the model will be performed to assess the model fit and to check for outliers.

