### Sample size

This is a naturalistic, observational project and therefore our sample size estimates are based on patient throughput and human resources. Based on these factors, we estimate to recruit up to 600 patients at baseline in the first year of the project. Using existing drop-out rates from SLaM IAPT services, we expect a drop-out rate of approximately 28%, leaving us with a sample of 472. According to power calculations, with power set at 0.8 and alpha at 0.05, this will allow us to detect standardised effect sizes of 0.13 in linear regression models estimating the effects of baseline factors in recovery. This is considered to be clinically significant; for example, a recent study of predictors of recovery [8] in the same setting showed that baseline PHQ-9 and GAD-7 scores were independently associated with recovery rates in a multiple regression model, with effect sizes ranging 0.14-0.21.

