### Measures

#### **
*Predictor variables*
**

The final choice of clinical and psychological predictors was based on discussions over a series of meetings with a large multidisciplinary group of academic experts, a systematic review of the literature conducted by the project coordinator (NG) and discussion over 3 subsequent meetings with the core Steering Committee who are all co-authors of this paper. The final list, which was reached by group consensus, has been considered comprehensive while at the same time manageable within a target completion time of 90 minutes for the whole assessment. This was judged to be the maximum time that we could impose on participants. Pilot work with the interview has confirmed that this is a realistic estimate of the time needed for completion.

PROMPT is collecting biological data as part of the National Institute for Health Research (NIHR) BioResource for Mental Health, which aims to enrol and collect biological samples from 52,000 healthy volunteers, patients and relatives. For PROMPT, this includes blood processed for DNA, RNA, buffy coat, serum and plasma. This sampling protocol allows for testing of an extensive battery of biomarkers relevant to treatment response in psychiatric disorders, and which are being routinely tested in a number of ongoing studies on a range of diagnostic categories. The BioResource project has separate ethical approval for the collection, storage and analysis of biological samples.

Demographic and patient characteristics are shown in Table 1. Table 2 shows the predictor variables, which will be collected at the baseline interview.

**Table 1 T1:** Demographic and treatment factors

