The primary outcome for PROMPT will be symptom change for depression and anxiety, as measured nationally by IAPT using by the PHQ-9 (Patient Health Questionnaire) and GAD-7 (Generalised Anxiety Disorder assessment) [25,26]. The PHQ-9 is a self-administered scale covering nine symptoms of depression, which are rated from 0 “not at all” to 3 “nearly every day”. With a sample of patients from primary care, the scale was found to have good reliability (Cronbach’s alpha = 0.89) and sensitivity and specificity of 88% [25]. The GAD-7 is a seven item self report measure, rated from 0 “not at all” to 3 “nearly every day”. The scale has good reliability (Cronbach’s alpha = 0.92) and sensitivity of 89% and specificity of 82% [26].

Both these measures are routinely collected as part of standard IAPT practice at every treatment session. Data will be gathered from the IAPT patient records system (IAPTus) with prior consent of participants. A score of 10 or more on the PHQ-9, and a score of 8 or more on the GAD-7 indicates caseness [25,26]. Participants who score above these thresholds for caseness on both the PHQ-9 and GAD-7 at their final appointment, will be defined as being in the ‘non-recovered’ group. The standard IAPT measure of Reliable Change Index will also be used as an outcome measure of treatment response which will be based on a drop of 6 points for the PHQ-9 and a drop of 5 points for the GAD-7 [27].

Secondary outcomes will be employment status, benefits status, engagement with services, and work and social functioning. Employment and benefits data is routinely collected at each IAPT appointment and entered on to the patient records system. Measures of engagement with IAPT services will include failure to engage, drop-out or discharge. Work and social functioning is measured using the Work and Social Adjustment Scale, a five item self-report measure collected as part of the routine IAPT outcome measures. This information will be collected from the care pathway of the patient records system IAPTus, which is routinely updated by IAPT clinical and admin staff.

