Whilst one of the strengths of this project is its naturalistic nature, this also presents some challenges in terms of the analysis of outcome data. In large scale randomised controlled trials that compare efficacy of different therapies, or medication vs therapy, manualised therapy is often used. Therapists in such studies will be supervised more closely than in standard practice, will be less free to vary sessions and will have their skills monitored. This project will involve therapists from different backgrounds including but not limited to; trained CBT therapists; clinical psychologists with IAPT high intensity therapy training and psychological well-being practitioners both pre- and post-qualification. These therapists will also have different amounts of experience and bring their own styles and ways of working to their patients. All of this will contribute to the variance in non-specific therapeutic factors influencing outcomes. At this point, we have not identified an efficient way of measuring these important ‘therapist factors’ but we will be working with team leaders in order to capture this in future research.

It is possible that patients who agree to take part in the project may not be representative of the IAPT population as a whole. Data will be available for participants who do not consent to take part in the main research program so it will be possible to compare participants with non-participants on standard factors such as demographics and initial PHQ-9 and GAD-7 scores. However, it is possible that other factors may prevent some people from agreeing to take part in the research such as health literacy, previous experience of psychological therapy and employment status. Due to the variability both in the participants, the therapists and also the therapy offered, the project will rely on a large sample size to detect clinically significant effects.

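### The models for independent predictors do not name initial PHQ-9 and GAD-7, so a marker of entry severity can pass as a predictor of outcome

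*Protocol article*

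**What the plan says.** The Analysis section of the protocol article describes the main models: "The independence of associations between the proposed predictor variables and IAPT non-response will be explored using linear mixed model methods" for continuous outcomes, and logistic regression for recovered versus non-recovered. It adds sex interactions and non-linear effects but names no adjustment covariate.

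Under Measures, Predictor variables, the list is presented as settled: "The final list, which was reached by group consensus, has been considered comprehensive while at the same time manageable". The same section says: "Table 2 shows the predictor variables, which will be collected at the baseline interview". Table 1 (demographic and treatment factors) and Table 2 list neither PHQ-9 nor GAD-7. Sex is in neither table.

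Under Outcome measures the two scales are outcomes: "The primary outcome for PROMPT will be symptom change for depression and anxiety, as measured nationally by IAPT". The binary outcome is an absolute threshold at the end of treatment: "Participants who score above these thresholds for caseness on both the PHQ-9 and GAD-7 at their final appointment" form the non-recovered group. Reliable change is a drop of 6 points on PHQ-9 and 5 on GAD-7.

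The Sample size section refers to an earlier study in the same setting in which "baseline PHQ-9 and GAD-7 scores were independently associated with recovery rates in a multiple regression model", with effect sizes of 0.14 to 0.21. The starting scores exist: "Both these measures are routinely collected as part of standard IAPT practice at every treatment session". Apart from that reference, the article mentions them only in the Discussion, which plans to compare participants with non-participants on "demographics and initial PHQ-9 and GAD-7 scores".

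**The concern.** Objective 4 is to establish longitudinal predictors of response, and the models are meant to show independent association. The two variables that the article itself cites as independently prognostic are not on the list of variables to be modelled.

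The outcomes make this matter. Entry requires acceptance by the service and capacity to consent, not caseness. A patient who starts below the thresholds and does not change is therefore not counted as non-recovered. A patient who starts below 6 on PHQ-9 or below 5 on GAD-7 cannot show reliable change on that scale. Starting severity thus pushes the two kinds of outcome in opposite directions.

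Self-criticism, childhood trauma, quality of life, personality and illness perceptions plausibly correlate with symptoms at entry. Without initial scores in the model, such a variable could be reported as an independent predictor when it only shows who started worse. Treatment targeting built on it would add nothing to the scores the service already holds.

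**Working it through.** **1. The plan's own figure.** Inputs from the Sample size section: N=472, power 0.8, alpha 0.05. The two-sided detectable correlation is tanh((1.960+0.842)/√(472−3)) = tanh(0.1294) = 0.129. Power at 0.13 is 80.8%. The stated 0.13 is reproduced as a two-sided test without covariates (one-sided gives 0.114). As a separate matter, 600 × (1−0.28) = 432, not 472. I use the stated 472 and check 432 below.

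**2. A pure severity marker.** Let B be the initial score, Y the final score and X a candidate predictor, all with SD 1. Let corr(X,B)=ρ and corr(B,Y)=b, with no effect of X on Y once B is known. Then, without adjustment:

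- corr(X, Y) = ρb
- corr(X, Y−B) = −ρ√((1−b)/2)

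The documents give neither correlation. Assumptions: ρ from 0.2 to 0.5; b=0.2, which treats the cited 0.14 to 0.21 as correlations and takes a value near the top; and b=0.5 as a stronger case.

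At b=0.2, corr(X,Y) runs from 0.2×0.2=0.04 to 0.5×0.2=0.10. Correlation with change (final minus initial) runs from −0.2×0.632=−0.126 to −0.5×0.632=−0.316. The same marker seems to predict a worse final score and a larger improvement.

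**3. How often it is declared significant.** Simulation, 1000 runs per cell, N=472, nominal 5%, X as the only predictor. Logistic recovery is a median split of Y.

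| b | ρ | Final score | Unadjusted change | Logistic recovery |
|---|---|---|---|---|
| 0.2 | 0.2 | 12.0% | 79.5% | 8.9% |
| 0.2 | 0.3 | 27.4% | 98.5% | 20.5% |
| 0.2 | 0.4 | 38.4% | 100% | 26.3% |
| 0.2 | 0.5 | 59.7% | 100% | 41.2% |
| 0.5 | 0.2 | 57.2% | 59.0% | 39.7% |
| 0.5 | 0.3 | 89.6% | 89.9% | 74.3% |
| 0.5 | 0.4 | 99.4% | 98.9% | 91.5% |
| 0.5 | 0.5 | 99.9% | 100% | 99.1% |

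With B in the model the rates are 4.2-6.8% (final score) and 3.5-5.9% (logistic). Adjusting change for B gives the same test of X as adjusting final score for B. At N=432 and b=0.2 the unadjusted rates are 13.3-54.0% and 10.0-35.8%, the same pattern.

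**4. Cost in power.** With B in the model, the detectable standardised coefficient is (1.960+0.842)·√((1−R²)/(N(1−ρ²))), where R is the correlation of initial score with outcome. At N=472 and ρ from 0.2 to 0.5:

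- R=0.3: 0.126 to 0.142
- R=0.5: 0.114 to 0.129
- R=0.2: 2.802·√(0.96/(472×0.96))=0.129 to 2.802·√(0.96/(472×0.75))=0.146

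The unadjusted value is 0.129.

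**The case against.** The strongest reply is that this is silence, not a decision. The Analysis section names no covariate for any model, the article is condensed, and an analysis plan that is not shown could add these scores. Table 2 holds what is collected at the baseline interview, whereas PHQ-9 and GAD-7 come from the service record, so their absence may reflect data source. Sex is also in neither table although sex interactions are planned, so the tables cannot be the full set of model terms.

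Much of this stands. A reader might infer that the plan rules out adjustment for initial severity; the text does not say so. What remains is that the article ties its independence claim to a list it calls final and comprehensive, and that list lacks the predictors used to justify the sample size.

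The size is also open to challenge. A reader might infer that false findings are near certain. Rates of that order on final score or recovery need an initial-final correlation well above 0.2, for which the documents give no figure. The simulation has one predictor per model; MINI diagnosis, EQ-5D with its mood item, or illness perceptions in a joint model would absorb part of the severity. A median split is also not the article's rule of caseness on both scales.

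A reader might further infer that a severity marker would predict non-response on every outcome. On unadjusted change, which matches the wording of the primary outcome, the bias runs the other way.

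Finally, adjustment is not neutral. Severity may lie on the path from a factor such as childhood trauma to outcome. In a session-level mixed model the first score may already be part of the outcome. Both points limit the remedy but do not remove the problem, and the mixed-model point does not help the logistic model.

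**Conclusion.** The point holds as a specification that should be corrected, not as proof that the planned results would be wrong. Followed as written, the models can present a pure marker of entry severity as an independent predictor: of non-recovery on the final-score threshold, and of greater improvement on unadjusted change.

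Under the weaker assumption (initial-final correlation 0.2), the single-predictor error rate at N=472 is about two to twelve times nominal for final score and about two to eight times for logistic recovery. For these outcomes it rises with a stronger initial-final correlation and falls if other modelled predictors carry part of the severity. The directions of bias follow from the outcome definitions provided that the predictor rises with severity and initial and final scores are positively but imperfectly correlated. The magnitudes rest on the assumed correlations and, for change, on equal SDs.

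**What to change.** State in the Analysis section that the logistic models (recovery and reliable change) and any model of final or change score include pre-treatment PHQ-9 and pre-treatment GAD-7, both continuous, and sex. Report each candidate predictor's effect over and above these.

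For a linear mixed model on session-level scores, choose one of two forms and write it down. Either take the first score as a covariate and remove it from the outcome series, or keep it in the outcome and test predictor-by-time terms. It should not serve as both.

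Show unadjusted associations alongside, so that factors for which severity may be on the path can be read both ways.

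The cost is wording and a few model terms. The symptom scores are already recorded; sex should be added to Table 1, since its interactions are planned. The detectable effect at N=472 moves from about 0.129 to between 0.114 and 0.142 if initial score correlates 0.3 to 0.5 with outcome, and to at most 0.146 if it correlates only 0.2.

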## Discussion

The project outlined in this paper aims to identify factors that predict response to psychological therapy in a primary care setting. Psychological therapy for depression and anxiety is currently recommended as a first-line therapy by clinical guidelines [6], yet is currently only available to 10-15% of sufferers [7]. Better targeted services are needed as access is unlikely to increase significantly and it is also currently uncertain to what degree the new Clinical Commissioning Groups will fund IAPT schemes. Outcome data currently available suggest that over half of patients are not meeting nationally recognised recovery rates [8]. At present there have been no other large-scale, naturalistic studies investigating predictors of outcome in an IAPT setting. The IAPT setting is particularly applicable to research, as patients are required to complete standard measures of mood and functioning at each contact. This project aims to embed recruitment practices in to an IAPT service allowing further studies to be carried out in the future. A secondary aim of this project is be extend the research to other IAPT sites.

Participants will complete therapy in a real world clinical setting allowing collection of meaningful observational data. Participants will be interviewed before beginning treatment, thus allowing collection of baseline data which can be used to predict future treatment outcome. Because of the nature of the outcome measurement in IAPT, participants will not need to attend for a second research interview as this information can be collected from the IAPT electronic patient records system. The numbers of patients attending for psychological treatment at IAPT services has been steadily increasing, such that, this is now the commonest route of talking therapy for mild to moderately affected people. A large scale research study investigating predictors of treatment response in this setting is therefore essential.

Collecting data from participants in a naturalistic setting, whilst providing ecologically valid data, is not without its limitations. We can anticipate around 30% drop-out of patients during IAPT therapy, meaning that we will lose some final outcome data for many patients we see at baseline. However, as data is collected on every contact, with a national completion rate of 90%, this will be minimised as we will be able to use data from the final session attended. This also affords us the opportunity to investigate if there are common factors that may explain drop-out. IAPT therapy is not standardised and this will introduce variability within our sample. Patients may receive one-to-one cognitive behavioural therapy with a trained CBT therapist, or a clinical psychologist. They may also receive guided self-help with a psychological well-being practitioner. Further, patients may attend for group therapy or psycho-educational workshops. Increasingly, IAPT services are offering alternatives to CBT including but not limited to; interpersonal psychotherapy, couples therapy, and eye movement desensitization and reprocessing therapy.

IAPT services are accessed by a wide variety of patients, with a diverse range of presenting complaints. The project will initially focus its recruitment on one borough (Southwark) whose services are currently provided by South London and Maudsley NHS Foundation Trust. In terms of ethnic diversity, the Office for National Statistics reported that the population of Southwark comprises 62% from White groups, 27% from Black groups and 11% from other groups. There will also be variety in use of prescribed medication amongst the participants, and this information is not always routinely collected within IAPT services. To overcome this, participants will be asked about their prescribed medication at the research interview. However, it will not be possible to monitor any changes in dosage or medication when looking at outcomes following treatment. As part of the standard IAPT data collection, participants are asked if they are prescribed medication, and if they are currently taking their medication. It is possible that a participant may change dose or even drug whilst receiving therapy.

Whilst one of the strengths of this project is its naturalistic nature, this also presents some challenges in terms of the analysis of outcome data. In large scale randomised controlled trials that compare efficacy of different therapies, or medication vs therapy, manualised therapy is often used. Therapists in such studies will be supervised more closely than in standard practice, will be less free to vary sessions and will have their skills monitored. This project will involve therapists from different backgrounds including but not limited to; trained CBT therapists; clinical psychologists with IAPT high intensity therapy training and psychological well-being practitioners both pre- and post-qualification. These therapists will also have different amounts of experience and bring their own styles and ways of working to their patients. All of this will contribute to the variance in non-specific therapeutic factors influencing outcomes. At this point, we have not identified an efficient way of measuring these important ‘therapist factors’ but we will be working with team leaders in order to capture this in future research.

It is possible that patients who agree to take part in the project may not be representative of the IAPT population as a whole. Data will be available for participants who do not consent to take part in the main research program so it will be possible to compare participants with non-participants on standard factors such as demographics and initial PHQ-9 and GAD-7 scores. However, it is possible that other factors may prevent some people from agreeing to take part in the research such as health literacy, previous experience of psychological therapy and employment status. Due to the variability both in the participants, the therapists and also the therapy offered, the project will rely on a large sample size to detect clinically significant effects.

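### Scoring recovery at the last attended session mixes drop-out with non-response, so a factor related only to attendance can appear to predict non-recovery

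*Protocol article*

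**What the plan says.** Four places in the protocol article bear on this point.

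- **Discussion.** "We can anticipate around 30% drop-out of patients during IAPT therapy". The authors accept that some final outcome data will be lost, but add that "this will be minimised as we will be able to use data from the final session attended". They give a national completion rate of 90% for data collected at each contact.
- **Outcome measures.** A participant is non-recovered if both the PHQ-9 and the GAD-7 are in the case range at the last appointment. No minimum number of sessions is set, and planned and unplanned endings are treated alike. Reliable change (a fall of 6 points on the PHQ-9, 5 on the GAD-7) is a further response outcome. Drop-out is also a secondary outcome: "Measures of engagement with IAPT services will include failure to engage, drop-out or discharge".
- **Sample size.** "we estimate to recruit up to 600 patients at baseline in the first year of the project"; then "we expect a drop-out rate of approximately 28%, leaving us with a sample of 472". With this number the study is said to "detect standardised effect sizes of 0.13 in linear regression models estimating the effects of baseline factors in recovery".
- **Analysis.** Linear mixed models are planned for continuous outcomes and logistic regression for recovered against non-recovered. Missing data and reasons for drop-out will be reported. The section does not say which session scores enter the mixed model, or whether drop-outs enter the recovery model.

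**The concern.** The project's main question is which baseline factors predict lack of response to therapy. The article treats drop-out as something distinct: it is its own outcome, and the Discussion plans to look for factors that explain it. The binary recovery outcome then joins the two, because a person who stops early is judged on a score taken before the full course could act.

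The last attended score is a real observation, but it does not stand in for the missing end-of-treatment score. Using it fills the gap in the data set while changing what the outcome measures. A factor that only makes people stop attending would then show an association with non-recovery. The article hopes its results will guide clinical decisions and new interventions, and a problem of attendance calls for a different response from a problem of treatment that does not work.

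**Working it through.** **1. The plan's own numbers.** Inputs from Sample size: 600 recruited, 28% drop-out, 472 remaining, power 0.80, alpha 0.05 (two-sided assumed), effect 0.13. The smallest detectable correlation is r = tanh[(z₀.₉₇₅ + z₀.₈₀)/√(n − 3)], with 1.960 + 0.842 = 2.802.

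- n = 472: tanh(2.802/√469) = 0.129. The stated 0.13 is reproduced.
- 600 × (1 − 0.28) = 432, so the printed 472 does not follow from its own inputs.

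| Treatment of drop-outs | n | Detectable r | Power for 0.13 |
|---|---|---|---|
| Removed (28%) | 432 | 0.134 | 77.3% |
| As printed | 472 | 0.129 | 80.8% |
| All kept through the last session | 600 | 0.114 | 89.2% |

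If the 90% completion rate is applied per patient, which is an assumption, the last row becomes 600 × 0.90 = 540, with r = 0.120 and power 85.8%.

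**2. The mechanism, in closed form.** Assume a binary predictor split 50/50 and 28% drop-out overall. Recovery is R_C in completers and R_D in drop-outs (at their last session), the same in both predictor groups. The predictor then acts on drop-out alone. With drop-out proportions q₀ and q₁, recovery in group j is (1 − q_j)R_C + q_jR_D.

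For a drop-out odds ratio of 2, q₀ = 0.211 and q₁ = 0.349 (mean 0.28). With R_C = 0.55 and R_D = 0.20:

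- group 0: 0.789 × 0.55 + 0.211 × 0.20 = 0.476
- group 1: 0.651 × 0.55 + 0.349 × 0.20 = 0.428
- odds ratio for non-recovery: (0.572/0.428)/(0.524/0.476) = 1.21 (1.22 from unrounded values)

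| Drop-out OR | R_C / R_D | Induced OR | Correlation | P(significant), n = 600 |
|---|---|---|---|---|
| 2 | 45% / 45% | 1.00 | 0.00 | nominal 5% |
| 2 | 50% / 30% | 1.12 | 0.03 | 0.10 |
| 2 | 55% / 20% | 1.22 | 0.05 | 0.22 |
| 2 | 60% / 10% | 1.32 | 0.07 | 0.39 |
| 3 | 50% / 30% | 1.19 | 0.04 | 0.18 |
| 3 | 60% / 10% | 1.54 | 0.11 | 0.75 |

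The pairs with unequal recovery keep overall recovery at 44% to 46%, close to the 45% quoted in the Background.

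**3. Simulation under the article's both-scales rule.** Assumptions: 600 participants, 28% drop-out, a standardised predictor with no effect on response, and drop-outs last seen after a given share of their full-course change.

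| Drop-out OR per SD | Share of change at last session | Induced OR per SD | False positives at 0.05 |
|---|---|---|---|
| 1.5 | 25% | 1.15 | 30% |
| 1.5 | 50% | 1.10 | 15% |
| 1.5 | 75% | 1.04 | 10% |
| 1.2 | 25% to 75% | 1.07 to 1.02 | 10% to 6% |

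At a drop-out odds ratio of 1.5, a completers-only analysis of the same data gave 4% to 6% false positives.

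**The case against.** **Two conflicting analysis sets.** A reader might infer that Sample size excludes drop-outs while the Discussion includes them, so that the article contradicts itself. The text does not support that. Sample size gives a planning number based on throughput and staffing and defines no analysis population. Planning on the number net of drop-outs and then using their partial data is conservative for power. What stands is that the number entering the recovery model is not clear.

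**Last observation carried forward.** A reader might apply this label to the whole plan. The article never says that a score is carried to a later time. Status at last contact is a legitimate endpoint for a service cohort, and preferring end-of-treatment status is a choice of what to estimate. The primary outcome is symptom change, and a mixed model fitted to every session's scores would carry nothing forward. What stands is narrower: the Discussion offers the last session as a remedy for lost final data, not as a different endpoint.

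**Early leavers are all non-recovered.** This too goes beyond the text. Non-recovery needs both scales in the case range, and caseness is not an entry criterion, so an early leaver may count as recovered.

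**Detail left to the full protocol or SAP.** Methods such as imputation can properly be left there. The finding concerns a rule the article does state and the benefit it claims for it. The separate drop-out outcome helps to detect the problem, but only if the two sets of results are read together, which the article does not say.

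**Conclusion.** The point holds for the binary recovery outcome, and for reliable change if that is scored at the same visit. Taking the last attended session as the outcome for interrupted therapy can make a predictor of attendance look like a predictor of non-response.

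The size is conditional. In the simulation the induced odds ratio per SD runs from 1.02 to 1.15 and false positives from 6% to 30%. The article supplies neither the strength of the predictor's link with drop-out nor how far drop-outs have improved when last seen. The results also depend on assumed score distributions, so they are illustrations and not limits. If drop-outs recover as often as completers, the bias is nil. In the closed-form examples the induced correlation (0.03 to 0.11 where recovery differs) stays below the planning effect of 0.13, yet it is often enough to give a significant result.

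A reader might also infer that keeping or removing drop-outs leaves the study underpowered. Keeping them raises power above the planned level. The shortfall at 432 comes from the arithmetic slip in Sample size, which is a separate matter. The harm here is misattribution.

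**What to change.** - **Symptom change:** state that the planned linear mixed model uses all session scores, with time and a predictor-by-time term.
- **Recovery (and reliable change, if scored the same way):** choose one of two definitions and say so. Either call the outcome status at last contact, or impute end-of-treatment status for drop-outs from their session scores and baseline data. In either case show the other definition and a completers-only analysis as sensitivity analyses.
- **Interpretation:** present predictors of non-recovery beside predictors of the drop-out outcome already planned, so that a factor working through attendance can be recognised.
- **Numbers:** state the n for the chosen set, with 432 in place of 472 if drop-outs are removed at 28%, and up to 600 if they are kept.

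The cost is wording and some extra analysis. The session scores are already in the service record, so no new data are needed. The mixed model and the imputation rely on data being missing at random given the observed scores and baseline data, and the report should say so.
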